## Abstract

**Background:**

Schizophrenia is among the world’s top 10 causes of long-term disability with symptoms that lead to major problems in social and occupational functioning, and in self-care. Therefore, it is important to investigate the efficacy of complementary treatment options for conventionally used antipsychotic medication, such as physical training, and psychosocial interventions.

**Objective:**

To combine aerobic and strength training with cognitive, emotional and social stimulation in one intervention for people with schizophrenia and test the feasibility and effects of this intervention.

**Methods:**

The study is a mixed-method randomized controlled trial to evaluate the effects of a 12-week intervention for adults with schizophrenia. The treatment group (30 participants) will receive the intervention in addition to standard care and the control group (30 participants) only standard care. The intervention consists of 24 biweekly sessions with a duration of 60 min. The pre-test (weeks from 4 to 2 prior to the intervention) and post-test (week 12) include clinical measure (PANSS), quality of life, social performance, movement quantity, brain function and eye tracking measures. In addition, a treatment subgroup of 12–15 participants and their family member or other next of kin will complete a qualitative interview as a part of their post-test. Two follow-up tests, including clinical, quality of life, brain function and eye tracking will be made at 6 and 12 months from the completion of the intervention to both study groups. The primary outcome is change in negative symptoms. Secondary outcome measures include general and positive symptoms, quality of life, social performance, movement quantity, brain function and eye tracking. Explorative outcome includes patient and family member or other next of kin interview.

**Results:**

Pilot data was collected by June 2023 and the main data collection will begin in September 2023. The final follow-up is anticipated to be completed by 2026.

**Conclusion:**

The InMotion study will provide new knowledge on the feasibility, efficacy, and experiences of a novel intervention for adults with schizophrenia. The hypothesis is that regular participation in the intervention will reduce clinical symptoms, normalize physiological measures such as brain activation, and contribute to new active habits for the participants.

**Trial registration:**

ClinicalTrials.gov, identifier NCT05673941.

## 1. Introduction

Schizophrenia is among the world’s top ten causes of long-term disability (GBD 2016 Disease and Injury Incidence and Prevalence Collaborators, 2017; Global Burden of Disease Collaborative Network, 2020). The major symptoms of schizophrenia include hallucinations, delusions, affective flattening, apathy and cognitive impairment. These symptoms lead to major problems in social and occupational functioning, and in self-care. Roughly 0.5–1% of the population is affected by schizophrenia, with similar rates across different continents, cultural groups, and sexes. The etiology of schizophrenia is not fully known but malfunctioning of the dopaminergic system is one of the leading hypotheses. Currently antipsychotic medications that modulate the dopaminergic system are exclusively the only available pharmacological treatment options for schizophrenia (Xu and Yang, 2022). However, treatment with antipsychotic medications is far from optimal in improving the symptoms of schizophrenia and can cause substantial adverse events that negatively impact patients’ physical health and quality of life (Stroup and Gray, 2018). While psychopharmaceuticals are effective in improving positive symptoms, their effectiveness on negative symptoms is limited. Therefore, it is important to investigate the efficacy of complementary treatment options, such as physical training and other psychosocial interventions, to reduce the impact of negative symptoms and enhance quality of life. Previous studies show promising effect of dance movement therapy or physical exercise on negative symptoms and quality of life (Röhricht et al., 2011; Lee et al., 2015; Dauwan et al., 2016; Martin et al., 2016; Gökcen et al., 2020). However, the transfer effects of such bodily interventions to cognition or emotion regulation, and their underlying brain processes, are studied to a lesser extent.

### 1.1. Physical training in people with schizophrenia

People with schizophrenia have a substantially lowered life expectancy, reduced cardiorespiratory and muscular fitness and increased risk of cardiovascular disease and metabolic syndrome in comparison to the general population (Vancampfort et al., 2015a,2016a,2017a; Sugai et al., 2016; Correll et al., 2017). They also have lower physical activity and higher level of sedentary lifestyle than the general population (Lahti et al., 2012; Crump et al., 2013; Vancampfort et al., 2017b). Eight systematic reviews have reported benefits of exercise for people with schizophrenia. The benefits cover general health outcomes, specific psychiatric symptoms and comorbid disorders (Soundy et al., 2014; Firth et al., 2015; Martin et al., 2017; Keller-Varady et al., 2018), cognitive functioning such as working memory, planning and problem solving (Sanada et al., 2016; Firth et al., 2017a,b) and cardiorespiratory fitness (Vancampfort et al., 2015b). However, some of these studies have been criticized for small sample sizes and poor reporting of the intervention characteristics. Overall, the systematic reviews highlighted that group exercises result in substantially better outcomes than solitary training (Firth et al., 2015, 2017a) and reduce the dropout rate (Firth et al., 2015; Vancampfort et al., 2016b). In addition, further improvements in outcomes and dropout rate could be seen when the interventions were facilitated by experienced professionals (Firth et al., 2015).

Mixed exercise program that combines aerobic, flexibility and resistance training is suggested to be effective in decreasing the symptoms of schizophrenia and increasing cardiorespiratory fitness and muscular strength (Martin et al., 2017; Girdler et al., 2019). However, studies suggest that better physical fitness is not associated with improved cognitive performance over 2 years, nor did the benefits on muscular endurance extend into a 3-month follow-up examination period (Cheng et al., 2017). There are also contradictory results regarding whether physical exercise interventions enhance plasma brain-derived neurotrophic factor (BDNF) in people with schizophrenia (Ikai et al., 2014; Kim et al., 2014; Kimhy et al., 2015; Firth et al., 2017b), which is suggested to be the underlying factor for the beneficial changes in brain structure and functional connectivity gained through exercise interventions for people with schizophrenia. The most consistent evidence suggests performing at least 150 min of moderate to vigorous aerobic exercise per week may be optimal in decreasing the symptoms of schizophrenia (Vancampfort et al., 2012).

### 1.2. Body awareness, emotions, and social cognition in people with schizophrenia

Expressive therapies, through dance, music or drama, emphasize the human body as the primary means of communication and expression (Sherwood, 2008). Dance movement therapy has been used for people with schizophrenia since 1940s initiated by Marian Chace and Trudy Schoop (Bryl and Biondo, 2021). Several techniques of dance movement therapy, like mirroring, body action and group interaction, have been used in enhancing body awareness, agency for own body, attention, and emotion recognition and regulation of people with schizophrenia (Bryl and Biondo, 2021). Qualitative, quantitative and mixed methods studies suggest that dance movement therapy can improve positive and negative symptoms of schizophrenia (e.g., Lee et al., 2015; Martin et al., 2016; Bryl et al., 2020; Millman et al., 2021).

Mirroring movement is a core technique of the Chacian approach on dance movement therapy in which the therapist creates empathic movement reflections in an interaction with the patient to connect deeply and authentically (Bryl and Biondo, 2021). Chace believed that by recognizing and recreating a meaningful gesture, posture, or simple movement at the right moment, trust in the therapeutic relationship could be established, which further, could lead to the patient’s willingness and ability to communicate difficult or repressed feelings and thoughts (Klingberg and Buchkremer, 2000).

Many people with schizophrenia suffer from symptoms of disembodiment, body image disturbances and deficits in the feeling of being an agent in their own bodies and lives (Priebe and Röhricht, 2001; Maggini and Raballo, 2004). Body image refers to a mental representation of the body which is influenced by several factors, like cognitive and affective variables, cultural and social norms and psychopathology (Slade, 1994). Body awareness refers to the perceptual capacity and the distinction between the information obtained from the sensory organs, like the proprioceptors in the muscles and joints. Body awareness also involves awareness of one’s inner feelings and ability to be attentive to their inner feelings and moods (Givehki et al., 2018). Agency includes the sensation that one causes their own action and the consequences of those actions (Renes et al., 2013).

Working with and enhancing body awareness, movement and agency for own body and action are the core elements dance movement therapy (Bryl and Biondo, 2021). In dance movement therapy with people with schizophrenia, it is documented that bodily disorganization, which is one of the positive symptoms of schizophrenia observed as unsynchronized or contradictory movements in various parts of the body, often mirrors cognitive disorganization and depersonalization (Wade et al., 2017). Negative symptoms, which include affective flattening, diminished expressiveness, reduced mobility, rigidity of movement and asociality (Wade et al., 2017), have been successfully alleviated with dance movement therapy (Röhricht et al., 2011; Lee et al., 2015; Martin et al., 2016; Gökcen et al., 2020). Qualitative results on basic body awareness therapy with people with schizophrenia show that good balance and posture are often connected with increased self-esteem and feelings of security (Hedlund and Gyllensten, 2010). The same participants also experienced an increased sensory awareness and ability to be more mentally present. They also reported to be in better contact with the surroundings.

For people with schizophrenia, a qualitative study on dance movement therapy suggested that group exercises through dance may transfer to their daily life (Bryl et al., 2020). In general, the group setting is commonly used in dance movement therapy (Klingberg and Buchkremer, 2000; Jones et al., 2012; Bryl et al., 2020). Creative movement in a group setting is shown to reduce negative symptoms and enhance symptom management and social connection in people with schizophrenia (Bryl and Biondo, 2021).

Research on dance movement therapy for people with schizophrenia suggests enhanced attention and self-regulation (Davis, 1981; Martin et al., 2016) whereas studies on exercise for people with schizophrenia report contrasting results on the benefits of exercise to cognition (Dauwan et al., 2016; Sanada et al., 2016; Firth et al., 2017a,b). In addition, the Chacian approach of dance movement therapy suggests that associations between movements and corresponding emotions can be used for emotion recognition and regulation (Bryl and Biondo, 2021).

Taken together, recent results suggest that dance-movement therapy and body psychotherapy may be effective in reducing both negative and psychotic symptoms in individuals with schizophrenia, as well as improve psychosocial functioning and ability to control anger (e.g., Lee et al., 2015; Martin et al., 2016; Bryl et al., 2020; Millman et al., 2021). In addition, recent qualitative results suggest that dance-movement therapy enhance interpersonal relationship skills, sense of social integration, emotional support, and coping strategy in symptom management (Bryl et al., 2020).

### 1.3. Brain and behavior

Behavioral and brain imaging studies may help to explain the bodily disconnection people with schizophrenia display. A disturbed implicit sense of the bodily self in people with schizophrenia is traced partly to deficits in the motor representation in the brain related to their bodily self (Ferri et al., 2012). The brain functions of people with schizophrenia also seem to have altered processes beyond motor regions. Ebisch et al. (2014) showed in their fMRI study that people with schizophrenia have an aberrant functional interaction of premotor cortex and insula with cingulate cortex. These brain regions are known to be central in mediating self-experience referring to one’s own subjective experience as opposed to objective observation of someone else’s experience. On the other hand, people with first episode psychosis show a disproportionally strong coupling between the posterior and anterior parts of the insula (Ferri et al., 2012). The former is related to awareness of bodily sensations through connection with sensorimotor cortex, and the latter is associated with the integration of cognitive and emotional responses (Damasio et al., 2000; Critchley et al., 2004; Craig, 2009). Taken together, these results suggest an imbalance in the processing between internally and externally guided information and its abnormal integration with self-referential processing in patients with schizophrenia.

Several empirical studies suggest that disturbances in self-experience and self-monitoring could be closely associated with anomalies in the self-other relationship (Ihnen et al., 1998; Blakemore et al., 2000; Voss et al., 2010). Because cortical midline and premotor regions also have complementary functions in relating the self to its social environment (Gallese, 2003; Johnson et al., 2006; Uddin et al., 2007; Caggiano et al., 2009), altered interactions between these regions likely also disrupt some aspects of social cognition. Indeed, people with schizophrenia with high self-monitoring skills were reported to have better social skills than the ones who showed lower self-monitoring skills (Ihnen et al., 1998).

Low tolerance for stress and stimuli is a common symptom within people with schizophrenia (Mc Gorry, 2005; Sestito et al., 2015). Results showing a similarity in facial muscle activation for smile and cry stimuli suggest that people with schizophrenia may have a disruption of the automatic, low-level processes related to facial mimicry (Sestito et al., 2013). Further, this disruption may foster their sense of detachment and increase disconnection between the “expressed” and the “felt” self (Aghevli et al., 2003; Sestito et al., 2013). This growing disconnection crucially creates a sense of distance—and even alienation—from their own experience, ending up in a scission and fragmentation within the self. One way how embodied interventions which include body awareness and/or emotional expression, such as dance-movement therapy or basic body awareness therapy, may improve the clinical symptoms of people with schizophrenia is by re-generating the connection to one’s own body and emotions.

### 1.4. Possible benefits of mixed physical exercise with creative movement in schizophrenia

Conventional occupational or physical therapy in people with schizophrenia does not include emotional expression. On the other hand, dance-movement therapy and body psychotherapy focus on emotional, social, cognitive, and physical integration of the individual. They do not primarily aim for the physical benefits that aerobic training, conducted at a moderate to intense level around 60% and higher of the maximum heartrate, is known to have. Nor do they aim primarily for gaining muscle strength, the training of which utilizes body weight with repetitions and progression in load and complexity over time.

There is a growing interest in the mechanics through which motor-related brain processes influence in emotional and cognitive processes. Several studies show how creative movement, such as dance, shapes the brain structure and function in both the general population and trained dancers (Karpati et al., 2015) and modifies the functions in the motor-related brain regions (Calvo-Merino et al., 2005; Cross et al., 2006, 2009; Pilgramm et al., 2010). These changes may occur through the dopaminergic and serotonergic systems, the function of which is shown to balance in physical and rewarding (joyful) activity, paired with the reduction of the stress hormones such as cortisol. Continuous movement and shared joy are characteristic for the creative physical exercise which might help to engage people with schizophrenia who tend to have low motivation for physical activity (Bryl et al., 2020; Bryl and Biondo, 2021).

Positive influence of regular dance training is shown to go beyond the improvement of physical abilities to the alleviation or prevention of symptoms in clinical populations. Different dance trainings in people with stroke, Parkinson or dementia are shown to increase physical abilities such as balance, muscle strength and smoothness of movement sometimes even more efficiently than conventional physiotherapy. Such dance trainings are also shown to improve quality of life, mood, emotional expression, and other behavioral measures (Hackney et al., 2012; [Bibr B3][Bibr B81]). In mixed exercise program with creative movement, bodily awareness, action and reaction are fundamental factors when adapting to the environment, music and the movement of the fellow-movers (Prabhjot et al., 2015; McKay et al., 2016). In addition to physical health, engaging with joyful creative physical exercise may improve the brain processes involved in cognition, emotion, self-awareness, social interaction, and behavioral adaptation.

### 1.5. Aims and expected results

The primary aim of the study is to investigate the effects of mixed exercise program with creative movement and cognitive, emotional and social stimulation as add-on to ongoing pharmacological treatment, in treating negative symptoms of schizophrenia. Previous studies with dance movement therapy, body psychotherapy or physical exercise show reduction in negative symptoms of schizophrenia (Röhricht et al., 2011; Lee et al., 2015; Martin et al., 2016; Gökcen et al., 2020), and that the change in these symptoms can be measured with PANSS (Röhricht et al., 2011; Lee et al., 2015; Sabe et al., 2020; but see but see also Bryl et al., 2020 for qualitative but not significant quantitative results). Thus, our hypothesis is that the intervention will improve negative symptoms detectable with PANSS in comparison to the control group. The reduction is anticipated to correlate with changes in brain function and physical measures. In line with previous studies (e.g., Röhricht et al., 2011; Lee et al., 2015; Curcic et al., 2017; Sabe et al., 2020), we will measure both negative and positive symptoms as well as general psychopathology, i.e., total PANSS score and look separately at the three symptom classes.

The secondary aim is to evaluate potential change in (a) general and positive symptoms of schizophrenia, (b) quality of life, depression and social performance (c) levels of physical activity, physical function and general health indicators, and cortical aspects of (d) error detection and conflict resolution on the prefrontal cortex, (e) emotional induction and regulation on specific emotions on the frontal cortex, (f) full-body movement quantity and rigidity, (g) cognitive function such as memory and fluency of speak, and (h) to explore the participants experiences of taking part in the intervention and any experienced change from it. Similarly, experiences from their related parties (a family member or other next of kin, nursing staff) will be collected regarding the influence of the intervention in the participants (Bryl et al., 2020). Our hypothesis is that, in comparison to the control group, the intervention group will show (i) strengthened physical health, function and reduced sedentary behavior, (ii) improvement in cognitive control and emotion regulation (Davis, 1981; Martin et al., 2016) and changes in their neural correlates (Balconi et al., 2015; Popov et al., 2019), and (iii) increased mobility and reduced rigidity in movement in the schizophrenia patients over the intervention (Bryl and Biondo, 2021) which can be also seen as increased fluidity and quantity of movement measured with Motion Capture (Poikonen et al., 2018).

## 2. Materials and methods

### 2.1. Approval and registration

The study was approved by the Swedish Ethical Review Board in Uppsala, Sweden (No. 2022-03980) and is registered on ClinicalTrials.gov (No. NCT05673941). Any protocol modifications will be communicated to relevant parties.

### 2.2. Study design

This study, called InMotion, will be conducted in two phases: pilot study and main study.

In the pilot study, which finished in June 2023, two people with schizophrenia participated in the intervention of mixed exercise program with creative movement (InMotion intervention) with 2–3 instructors. Participants did not need so many instructors, but the pilot study was a good chance also for the instructors to practice guiding the intervention. Hence, three instructors participated in some of the pilot sessions. A family member or other next of kin could attend the movement sessions if the patient wished so. The intervention lasted 12 weeks including 60-min sessions twice a week, similar to the following main study. The following pre- and post-intervention data was collected: PANSS, CGI-S, CGI-I, PSP, CDSS, BAQ, EQ5D, blood pressure, resting heartrate, breathing frequency, waistline, BMI, postural stability, leg strength and accelerometer/everyday activity. Cognitive and brain imaging data were not collected at this phase due to logistical issues with the EEG-fNIRS equipment. However, the brain imaging measurement will be piloted separately with a person with schizophrenia.

The main study will be a prospective randomized controlled trial (RCT) with 2 parallel groups: an intervention group (30 participants) and a control group (30 participants) of adults with schizophrenia or disorders with symptoms similar to schizophrenia, as described in section “2.3.1. Inclusion criteria.” The intervention consists of sessions on mixed exercise program with creative movement two times a week for 12 weeks in addition to standard medical care as described in section “2.9 Standard care.” Each group will include 4–6 participants under the guidance of two instructors. The control group receives standard medical care and gets access to the video-links after the 12-month follow-up. Most outcomes are measured at baseline, after 6 and 12 weeks, 6 and 12 months (see Figure 1 for details). At all follow-ups, data is collected for both the intervention and control groups. The timeframe of the main study is from autumn 2023 to spring 2025. The study adheres to the standard methodology of intervention research. This protocol is conducted according to the SPIRIT (Standard Protocol Items: Recommendations for Interventional Trials) guidelines (Chan et al., 2013). The study will be reported according to the CONSORT (Consolidated Standards of Reporting Trials) guidelines (Schulz et al., 2010), and COREQ (Consolidated Criteria for Reporting Qualitative Research; Tong et al., 2007).

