### 2.7. Sample size

The sample size is calculated according to the primary outcome PANSS. For the primary outcome (improved negative symptoms according to PANSS after 12 weeks), the total number of required study participants was calculated (Curcic et al., 2017). Calculation was based on a minimum improvement of 15% on total PANSS score between the intervention and control group. With a power of 80% and a significance level of 0.05, we calculated the sample size to be *N* = 60 (30 intervention + 30 control participants), including a 25% dropout rate.

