#### 3.3.3. Statistical analysis

The InMotion study follows the intention-to-treat paradigm. Complementary analyses will be performed per protocol according to the number of sessions the participant attends. For baseline statistics between the groups, descriptions will be constructed using frequencies and proportions for categorical data and means and standard deviations for continuous variables. Baseline characteristics will be compared using the Fisher exact test for dichotomous outcomes, the Mantel-Haenszel chi-square test for ordered categorical outcomes, and the Mann-Whitney *U*-test or unpaired *t*-test for continuous outcomes. A *P*-value of < 0.05 for the two-tailed test will be considered statistically significant for all outcomes. When deemed necessary, correction for multiple significance will be performed.

The primary outcome analysis will initially be performed using a Fisher exact test to evaluate differences between groups. To analyze the change in scores from baseline between groups for approximately normally distributed variables, a repeated-measures covariance pattern mixed model will be used, adjusting for significant differences at baseline. To identify predictive factors at baseline that might be associated with the primary outcome, a univariable logistic regression analysis followed by a stepwise multiple logistic regression analysis will be performed.

The distribution of continuous variables will be described using the mean and standard deviation or median and interquartile range. Categorical variables will be described with numbers and percentages.

The interviews will be analyzed by qualitative content analysis, to this day planned to be according to Hsieh and Shannon (2005); data from interviews will be transcribed verbatim, read through and analyzed into units. These units will be condensed and coded. The codes will be divided into categories and subcategories, and abstracted to overall themes if found. Latent meaning will be interpreted and the themes shall capture the core message of the whole data-material and will be strengthened with quotes. NVivo software program (QSR International; NVivo, 2022) will be used during the analysis.

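### Only the intervention arm is taught in classes of 4–6, and neither the mixed model as described nor the sample size allows for correlation between classmates

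*Protocol article*

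**What the plan says.** Section 2.2 describes delivery: "Each group will include 4–6 participants under the guidance of two instructors". Since the same section puts 30 patients in each arm, these groups are training classes, not trial arms. They meet twice a week for 12 weeks. The comparison arm has no such structure: "The control group receives standard medical care and gets access to the video-links after the 12-month follow-up".

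Section 2.7 sets the sample size. "Calculation was based on a minimum improvement of 15% on total PANSS score between the intervention and control group" gives the effect. "With a power of 80% and a significance level of 0.05, we calculated the sample size to be" leads to a total of 60 ("30 intervention + 30 control participants), including a 25% dropout rate"). No class size, ICC or design effect is among the inputs.

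Section 3.3.3 names two analyses that bear on the primary outcome. The first step is "The primary outcome analysis will initially be performed using a Fisher exact test to evaluate differences between groups". For change scores, "a repeated-measures covariance pattern mixed model will be used, adjusting for significant differences at baseline". Neither is described with a class or instructor term.

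Section 7 lists the supportive group setting and the instructors among the components that might explain a positive result. Table 1 and section 2.8 add partner and small-group mirroring between participants.

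**The concern.** Patients are randomised individually, but those in the intervention arm are then treated together and the controls are not. This is a partially nested design. Classmates share instructors, companions and sessions, and the protocol treats some of these as possible active ingredients. If their outcomes are positively correlated, 30 treated patients carry less information than 30 independent ones.

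A covariance pattern over visits models the correlation of one patient's repeated measurements. It leaves patients independent of each other unless class is added. The standard error of the arm difference would then be too small, the confidence interval too narrow, and the chance of a false positive on change in PANSS negative score above the nominal 5%. An analysis that does respect the classes would have less power than the stated 80%.

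**Working it through.** **Inputs from the protocol article.** Class size m = 4–6, one arm only (2.2). 30 per arm, 80% power, alpha 0.05, 25% dropout (2.7). Two-sided testing: the P-value threshold "for the two-tailed test will be considered statistically significant for all outcomes" (3.3.3). Number of classes: 30/6 = 5 to 30/4 = 7.5, so about 5 to 8.

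**Assumed, because the article does not give it.** ICC of 0.01, 0.05, 0.10 and 0.15.

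**Step 1: the plan's own figure.** N = 60 cannot be reproduced, since no SD or baseline mean is stated. It can be solved backwards under independence, with d = (1.960 + 0.842) × √(2/n):
- dropout as 30 × 0.75 = 22.5 evaluable per arm: d = 0.835
- dropout as 24 × 1.25 = 30: d = 0.809

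A 15% difference corresponds to these only if the SD is about 18–18.5% of the mean (0.15/0.835 = 0.180; 0.15/0.809 = 0.185). On either route the 60 patients are fully used before any clustering.

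**Step 2: cost of correlation alone.** The design effect DE = 1 + (m − 1) × ICC applies to the intervention arm only. The true SE divided by the unadjusted SE is r = √((DE + 1)/2). Power is Φ(2.802/r − 1.960), type I error of the unadjusted test is 2 × (1 − Φ(1.960/r)), and the total N that restores 80% is 60 × r². For m = 5:

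| ICC | DE | r | Power | Type I | N for 80% |
|---|---|---|---|---|---|
| 0.01 | 1.04 | 1.010 | 79.2% | 5.2% | 61.2, so 62 |
| 0.05 | 1.20 | 1.049 | 76.2% | 6.2% | 66 |
| 0.10 | 1.40 | 1.095 | 72.5% | 7.4% | 72 |
| 0.15 | 1.60 | 1.140 | 69.0% | 8.6% | 78 |

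Across m = 4 to 6, power is 77.1–75.2% at ICC 0.05 and 74.3–70.7% at ICC 0.10.

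**Step 3: simulation of a continuous outcome.** Treated patients receive a shared class effect, controls are independent, and an unadjusted t-test stands in for a model without a class term.
- 6 classes of 5 against 30 controls: type I error 6.0%, 7.3% and 8.3% at ICC 0.05, 0.10 and 0.15
- after dropout, 6 classes of 4 against 23: 5.7%, 6.7% and 7.5%
- across these and 5 classes of 6 against 30: 5.7–6.4%, 6.7–8.1% and 7.5–9.3% (repeat runs reached 9.7% for classes of six at ICC 0.15)
- at ICC 0.01: about 5.2%

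**Step 4: the Fisher exact test.** With the same class effects, the outcome dichotomised and response rates of 20%, 30% and 50% assumed, its type I error is about 2.5–5.2%. One set of runs touched 5.6% after dropout.

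**Step 5: an analysis that respects the classes.** Class means against individual controls with Satterthwaite degrees of freedom hold about 5%. With 6 classes of 4 against 24 controls, power is 71% at ICC 0.05 and 68% at 0.10. It is already 75% at ICC 0, so part of the fall from 80% comes from having only six classes. At a slightly larger assumed effect of 0.855 SD, against 23 controls, power is 75%, 72% and 68% at ICC 0.05, 0.10 and 0.15, and 78% at ICC 0.

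**The case against.** **The first-named primary test is Fisher's.** A reader might infer that the primary test exceeds 5%. For the Fisher exact test this is not supported: clustering raises its error rate, but the test is conservative enough at these sample sizes to absorb most of the increase. The inflation applies to the continuous mixed-model comparison.

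**No ICC is given.** This stands. At 0.01 the effect is negligible, and no source in the article favours a higher value. The statement must be conditional on positive correlation. What the article does supply is a reason to expect some, in its own account of how the intervention may work.

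**The power figures are soft.** This stands too. The effect size is back-solved, and part of the loss in a class-level analysis is a degrees-of-freedom cost that would arise with no correlation at all. It would be wrong to read any one power figure as established.

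**Each class might be thought to have its own instructors and a fixed membership.** The article says neither. It gives two instructors per class and a standardised programme, and does not say whether the same pair leads several classes. The point needs only that classmates share sessions and leaders.

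**An unseen analysis plan may add a class term.** It may, and the article does not exclude one. That would settle the model, but not the sample size as published, which lists its inputs without any allowance.

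**Conclusion.** The point holds in conditional form. The design is clustered in one arm, the mixed model as described does not cover that clustering, and the sample size makes no provision for it. For the comparison of change in PANSS negative score, any positive ICC makes the unadjusted standard error too small. The effect is trivial at 0.01, modest at 0.05 and material at 0.10–0.15.

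The loss of power from correlation alone is about 1 point at ICC 0.01, 4 points at 0.05 and 7–8 points at 0.10. A class-level analysis loses a few points more because there are few classes. These figures assume equal class sizes, a back-solved effect of about 0.81–0.84 SD and the stated ICCs, so they are indicative only. That the effect is expressed on total PANSS while the primary outcome is the negative subscale is a separate matter and is not needed here.

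**What to change.** 1. Record class membership for every intervention patient, most easily while classes are running.
2. Add to the mixed model a random class effect for the intervention arm only, with each control as a singleton, arm-specific residual variance, and Satterthwaite or Kenward-Roger degrees of freedom.
3. Make this model, not the Fisher exact test, the basis for the primary effect estimate and confidence interval.
4. Restate the power of N = 60 over an assumed ICC range, for example 0.01–0.15, applying the design effect to the intervention arm only. Applying it to both arms would overstate the problem.

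The cost is a few lines of model code and a paragraph of text. The price is a wider interval, a less favourable stated power, and a class variance that 5–8 classes estimate poorly. No extra patients are needed to correct the inference. Restoring 80% power is a different question: with classes of five and before the degrees-of-freedom cost, it would take about 66 patients at ICC 0.05 and 72 at 0.10. If recruitment stays at 60, the lower power should simply be stated.
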